## Introduction

## Background and Rationale

Since appearing as a cluster of patients with ARDS in the December of 2019 in Wuhan, China, COVID-19 caused by SARS-CoV-2 has rapidly spread worldwide, with pandemic status declared in March 2020.^1^ Currently there have been over 1.6million cases, with over 100, 000 deaths.^2^

SARS-CoV-2 is a β-coronavirus, an enveloped non-segmented positive-sense RNA virus.^3^

Sequencing has demonstrated that SARS-CoV2 is 79% identical to SARS-CoV, which caused the SARS (Severe Acute Respiratory Syndrome) epidemic in 2003, 50% with the MERS (Middle Eastern Respiratory Syndrome) coronavirus and 96% identical to a bat coronavirus.^4,5^ Analysis of 104 strains of samples taken between December and February demonstrated 99.9% homology, with little mutation, providing some hope for eventual vaccine therapy.^6,^ ^5^

The virus was first recognised in Wuhan, China. Though many of the initial cases were linked to a seafood market, a significant proportion of early cases did not have any association with the market, suggestive that human to human spread occurred in the month prior.^1^

In contrast to the related coronavirus respiratory diseases MERS and SARS, which were more frequently associated with nosocomial infections, COVID-19 spreads more avidly, via close contacts, with a household secondary attack rate of 3-5%.^7,6^ Early calculations of the reproductive number (R_0_) were estimated at 2.3-3.5.^8^ The viral load profile is similar to influenza, peaking early together with symptom onset, which could account for the higher transmissibility compared with SARS and MERS.^9^ The virus is spread through respiratory droplet and fomite spread in close proximity contact and via aerosolised procedures, a particular risk to health care workers. The virus has also been isolated in faecal samples, however no known cases of faecal-oral spread have been noted.^10,11^ Similarly to SARS-CoV, SARS-CoV-2 gains entry into respiratory epithelial cells via attachment to the ACE2 receptor.^4,12^ The clinical presentation and pathology resembles SARS and MERS, though with less upper respiratory and gastrointestinal symptoms.^13^ The estimated incubation period has a mean of 5 days, with the majority of cases developing symptoms by 14 days.^14^ However one study found 15.6% of patients had not developed symptoms by day 14 following exposure.^15^

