Within this initial planned cohort (**Study Flow Diagram 1, page 18**), a subset of ~400 staff members with confirmed symptomatic, PCR positive, antibody positive or equivocal, SARS-CoV-2 disease (and an additional 2100 staff sero-positive or equivocal staff members who were either PCR negative or asymptomatic) will be followed with intensive 1 to 2 monthly blood sampling to determine antibody titres to the SARS-CoV-2 specific protein using the *EDI^TM^* ELISA assay. Participants who are seropositive or equivocal will also have the option of providing an additional one off 20ml sample for T-cell assay analysis and a salivary sample for IgA analysis.

All 7000 recruited healthcare workers (2100 SARS-CoV-2 sero-positives and N~4900 seronegatives) will have blood taken for serological testing at baseline then at 6-monthly intervals for a total of 6 years. In addition to repeated serological testing, participants will continue as all healthcare workers at GOSH to have access to the staff testing program. This program tests symptomatic staff members by nasal swab PCR testing for SARS-CoV-2. Staff who have been tested for SARS-CoV-2 through the staff testing program will be consented for the PCR and serology results to be used in the study. All participants will also be asked to complete a detailed health and demographic questionnaire prior to each appointment, electronically. The technology design of the questionnaire will optimise participation. If key questions are missed, participants will be contacted by phone, text or email to optimise data collection and statistical analysis. As key factors impacting COVID-19 evolve, questions on review questionnaires will address these.

The data will enable us to determine the attack rate (percentage of healthcare workers with PCR proven infections/re-infections) and incidence (the rate of occurrence of disease) of SARS-CoV-2 infection amongst healthcare workers with and without antibodies. The comparison of the attack rate will indicate the protection antibodies provide. Further, the stratification of results by antibody titres, will provide information on whether a specific level of antibody confers protection.

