# Statistics

## Statistical methods to be employed (plan of analysis)

Antibody titres are expected to follow a negative exponential (log-linear) decay over time as seen following other respiratory viral infections. Serial antibody titres will be log-transformed and then multivariate linear regression models will be used to determine the predictors of antibody decay. Variable attack-rate between groups will be compared with a two-sample test of proportions and the incidence of COVID-19 disease between study groups will be compared using survival analysis with log-rank testing.

Fig.1: An estimated sample size of 4500-8000 total participants (with seropositive sample size of 1500-2700 participants, Fig.1, x-axis) provides 80% power at alpha 0.05 to detect an effect size of ≥17% decline in antibody titres over 12-months. This is based on a seropositivity prevalence of 33%, as observed in preliminary results so far and a negative exponential (log-linear) model of waning antibody titres, with 3 co-variate predictors of antibody decay, including sex, age and ethnicity (green line) or 4 co-variate predictors, including sex, age, ethnicity and co-morbidities (blue line). For comparison, the model was repeated based on 20% decline in baseline antibody titres over 12-months (using alpha 0.05), with the same 3 (orange line) or 4 (red line) co-variate predictors of antibody decline.

[figure not shown]

In order to determine the study power for varying effect sizes with unequal group sizes we undertook a two-sample power calculation of proportions with group sizes of 2100 seropositive cases and 4900 seronegative comparators using R (foundation for statistical computing) pwr function pwr.2p2n.test (Figure 2).

Figure 2. Power curve for group sizes of 2100 and 4900 participants showing that this study will have the power to detect an effect size of 0.07 i.e. a difference in the proportion in the attack rate between the two groups of 7%.

[figure not shown]

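### The Figure 2 caption reads Cohen's h = 0.07 as a 7-percentage-point difference in attack rate, overstating the detectable difference at least twofold

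*Protocol*

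**What the plan says.** The protocol's section on statistical methods (12.1) plans the comparison in one sentence: "Variable attack-rate between groups will be compared with a two-sample test of proportions". Section 7.1 defines the outcome as the "attack rate (percentage of healthcare workers with PCR proven infections/re-infections").

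For power, section 12.1 takes "group sizes of 2100 seropositive cases and 4900 seronegative comparators" and says the calculation was done "using R (foundation for statistical computing) pwr function pwr.2p2n.test". The Figure 2 caption gives the result as "an effect size of 0.07 i.e. a difference in the proportion in the attack rate between the two groups of 7" per cent.

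The caption gives no power, alpha or sidedness. The protocol gives no expected attack rate for either group. The only settings nearby belong to the antibody-decay calculation in Figure 1, which "provides 80% power at alpha 0.05 to detect an effect size of ≥17% decline in antibody titres over 12-months".

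**The concern.** The caption treats two different quantities as one. The function named works on Cohen's h, so the 0.07 it handles is not a difference in proportions. The absolute difference that a given h represents depends on the baseline attack rate, which the protocol does not state.

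This is the only power statement for secondary objective 2, the attack rate in staff with and without antibodies. Section 7.1 relies on that comparison to show how far antibodies protect. Anyone taking the caption at face value would think that a gap below 7 points is out of reach. They would dismiss a fall from 5% to 2%, which the design has ample power to detect. If the seronegative attack rate were below 7%, a 7-point reduction could not occur at all.

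**Working it through.** **Inputs.** n1 = 2100 and n2 = 4900 (section 12.1). Power of 80% and alpha of 0.05 are borrowed from the Figure 1 caption. Two-sided testing is assumed. Seronegative attack rates are scanned because none is given.

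**Step 1: reproduce the 0.07.**
- Cohen's h = 2·asin(√p1) − 2·asin(√p2).
- Power ≈ Φ(h·√(n1·n2/(n1+n2)) − z).
- √(2100 × 4900 / 7000) = √1470 = 38.34.
- Smallest h for 80% power, two-sided 0.05: (1.960 + 0.842)/38.34 = 2.8016/38.34 = 0.0731, which rounds to 0.07.
- One-sided, the smallest h is 0.065, which also rounds to about 0.07.

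So the printed 0.07 is what the named function gives as h.

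**Step 2: test the 7%.** Since p1 − p2 = sin(a + b)·sin(a − b), with a = asin√p1, b = asin√p2 and a − b = h/2, the difference can never exceed sin(h/2).
- For h = 0.07 the ceiling is sin(0.035) = 0.0350, or 3.5 points, whatever the baseline.
- A true 7-point difference needs h of at least 2·asin(0.07) = 0.140. Its power is then at least Φ(0.140 × 38.34 − 1.96) = Φ(3.41), about 99.97%.

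Seven points is therefore far above the detection limit at every baseline.

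**Step 3: what h = 0.07 means.** Back-transform with p(seropositive) = sin²(asin√p(seronegative) − 0.035):

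| Seronegative attack rate | Seropositive rate at h = 0.07 | Difference (points) | 7 ÷ difference |
|---|---|---|---|
| 50% | 46.5% | 3.5 | 2.0 |
| 30% | 26.8% | 3.2 | 2.2 |
| 20% | 17.3% | 2.7 | 2.6 |
| 10% | 8.0% | 2.0 | 3.5 |
| 5% | 3.6% | 1.4 | 4.95 |
| 2% | 1.1% | 0.9 | 8.1 |
| 1% | 0.4% | 0.6 | 12 |

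(The ratios use unrounded differences.)

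**Step 4: cross-check without the arcsine scale.** A pooled two-sample z-test at 80% power and two-sided 0.05 gives detectable differences of 3.65 points at 50%, 2.85 at 20%, 2.1 at 10% and 1.5 at 5%. The conclusion does not depend on the transformation.

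**Step 5: the 5% versus 2% example.** h = 2 × (0.2255 − 0.1419) = 0.167, and power = Φ(0.167 × 38.34 − 1.96) = Φ(4.45), above 99.9%.

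**Step 6: could 7% mean a relative reduction?** At a 50% attack rate, 3.5/50 = 7%, so it fits there. At 10%, h = 0.07 is 2.0/10, a 20% relative reduction. The caption also speaks of a difference in proportion. This reading does not rescue it.

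**The case against.** The strongest reply is that the mistake is harmless. It makes the study look less sensitive than it is. It concerns a secondary objective, while the primary objective has its own calculation in Figure 1. The planned two-sample test and log-rank test are unchanged. All of that stands, and it limits the severity. It does not make the stated figure right.

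Some stronger readings are tempting, but the documents do not support them:

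- **Sizing or stopping decisions are wrong.** No such decision uses 7%. The only early-stopping condition, in Definition of End of Study, is that all participants have undetectable antibodies. The synopsis makes recruitment depend on logistics, funding and demand, so power was worked out from an available sample. Subject Withdrawal Criteria mentions recruiting more to lower the detectable effect, but only if funding allows and with no threshold.
- **There is a second error because h = 0.07 gives only 76.5% power.** That figure assumes two-sided alpha 0.05. One-sided power is 85.1%, the caption states no target power, and 0.073 rounds to 0.07.
- **The overstatement has an upper limit of about 5.** That holds only for seronegative rates of about 5% or more. The protocol gives no rate, and the factor is about 8 at 2%.
- **The 3 to 5% household rate in Background and Rationale fixes the baseline.** It describes household contacts in published work, not PCR-proven infection in this cohort.

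**Conclusion.** Wrong as written; moderate severity. The 7-point detectable difference is too large by a factor of at least about 2 at any attack rate, and by about 3.5 at 10%, 5 at 5% and 8 at 2%. The minimum factor of 2 follows from h = 0.07 alone and needs no assumption about alpha, power or baseline. The larger factors depend on the seronegative attack rate, which the protocol does not give.

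Identifying 0.07 as the 80%-power value of h rests on the Figure 1 settings, on two-sided testing and on rounding. The Figure 2 curve was not available to check.

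A reader might infer that the study is underpowered for this comparison. The misreading gives no ground for that: with the planned group sizes, power for 7 points is about 99.97% or more before any attrition.

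**What to change.** In the Figure 2 caption, delete the clause that turns 0.07 into a 7% difference and label the effect size as Cohen's h. State the power, alpha and sidedness actually used. Then give the detectable difference as pairs of attack rates over a range of assumed seronegative rates.

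If the settings were 80% power and two-sided alpha 0.05, which the sponsor must confirm, then h = 0.073. With the full 2100 and 4900 and no attrition, the pairs are:

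| Seronegative (assumed) | Seropositive, detectable |
|---|---|
| 2% | 1.1% |
| 5% | 3.5% |
| 10% | 7.9% |
| 20% | 17.2% |

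The cost is one caption and a four-row table at the next amendment. Recruitment, follow-up and the planned tests do not change.

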# Data Management

## Source Documents

The study will not require access to any of the participants medical records as part of this research. Instead new recruits will be asked to help complete an online questionnaire about their health, symptoms and exposure to SARS-CoV-2. Systems already employed by Occupational Health at GOSH have been duplicated to allow data collection of on online questionnaires on GOSH secure servers. This process has an established system of governance approved by GOSH ICT department. No hard copies of the identifiable data will be downloaded. The laboratory data will be stored as for existing occupational health medical information (such as Hepatitis B serology) which are stored on a secure NHS trust laboratory server. Samples will be stored in -70C freezers with a laboratory number unliked from any patient identifiers. Only named study staff will have access to the data. On all study-specific documents, other than the signed consent, the participant will be referred to by the study participant number/code, not by name.

## Direct Access to source data / documents

Only members of the study research team and authorised representatives from the sponsor will have direct access to the source data and study documentation. All source data and study documentation will also be available to external auditors if and when required, and inspections in the event of a regulatory inspection. Access to the final data set will remain with the chief investigator and co-investigators.

## Data Recording and Record Keeping

After providing informed consent, participants will be provided with a link to an online study questionnaire. This will be stored on GOSH secure servers and completed prior to staff phlebotomy appointment. Only named study staff will have access to the raw data. As soon as possible after collection identifiable data will be stored in a separate database to medical data. The data will be linked only by a study ID to which only named study staff will have access to. Data will be retained for the 6 year duration of the study after which it will remain pseudonymized for internal use and future research and completely anonymized for sharing with research collaborators or publication.

## Archiving

Archiving will be authorised by the Sponsor following submission of the end of study report. We will also submit the complete but anonymized dataset to a secure and publicly available database such as Dryad (used by PLOS Medicine) to enable access to other researchers. Essential study documents will be retained for a 30 years after completion of the study. These documents will be retained for longer if required by the applicable regulatory requirements.

# Patient Confidentiality & Data Protection

Participant identifiable data, including name, date of birth, email and telephone number will be required for the registration process. Entering all data to an online database on a secure trust server will ensure the highest level of security available to minimize the risk of a breach in confidentiality. Identifiable data will be stored with a study ID separately to a linked database with medical data. All documents will be stored securely and only accessible by study staff and authorised personnel. The study will comply with the Data Protection Act 2018, which requires data to be anonymised as soon as it is practical to do so at the end of the study.

# Sample Collection, Storage, Transfer and Analysis

Blood samples will be collected by trained phlebotomists, nursing staff, doctors or medical students. Once informed consent has been provided and the online questionnaire is complete, appointments will be made with the study phlebotomy clinic. The phlebotomy clinic will be initially located in the outpatients clinic area as it is currently vacant due to the pandemic. When outpatient appointments resume, we will resume testing in a designated part of the hospital with equivalent facilities. Each appointment will be 15-20 minutes long in order to prevent unnecessary mixing between staff. Using an aseptic technique with alcowipes, a vacutainer system, a 21 guage green needle and a tourniquet, a 4ml sample of blood will be taken in a BD Vacutainer Serum Separating Tube (SST) Advance Tube and a 4ml sample will be taken in an BD Vacutainer EDTA tube. For seropositive and equivocal participants who further consent, an additional 20ml blood sample will be taken for T-cell assay and tissue typing, in EDTA tubes and approximately 4ml of a salivary sample for IgA assay. For blood samples a cotton wool ball will be used to prevent bleeding and 1cm circular plaster applied. For whole saliva samples, participants will be asked to passive drool (the gold standard sample), unstimulated, into polypropylene cryovials. The samples will be transported in a sealed specimen transfer box to the Camelia Botnar laboratory at Great Ormond Street in batches twice per day and be stored at -4^o^C in restricted access fridges until sample processing. Those samples arriving in the laboratory in the late afternoon will be processed the following morning, while those samples arriving from the morning batch will be processed the same day. All samples will be given a laboratory code on arrival and entered into the secure Beaker system database under this laboratory code. It is possible to batch up to 45 samples in duplicate on each run, using our DS2 automated ELISA processing system from Dynex Technologies. Each sample will be tested using the *EDI^TM^* diagnostic assay which detects the optical density of antibodies in serum samples to the specific protein SARS-CoV-2. IgG antibodies to the specific protein will be tested and reported. As and when new ELISA assays with superior performance become available, we will test them using our sample bank of positive and negative controls before considering replacing our current gold standard assay. This applies particularly to ensuring study alignment in our collaboration with the SIREN study at Imperial College who use different serological assays. Neutralization assays will also be undertaken in appropriate P3 biosafety laminar flow cabinets in order to determine the in-vitro correlates of antibody protection. Cell mediated immune responses to purified spike protein will also be tested for study participants using ELISPOT or flow cytometry. This will enable us to determine the titres of antibody associated with a 50% reduction in viral plaques and the relevance of cell mediated immunity on future reinfection. This work will be lead by [name] and [name] who both have 20 years experience of developing, evaluating and standardizing new immunological assays in the laboratory. In order to improve capacity of antibody testing for this study, the WHO Reference Laboratory for Pneumococcal Serology, a GCLP accredited laboratory  run by [name] and based in the Great Ormond Street Institute of Child Health will be used. A panel of +ve and -ve samples have been assessed in both laboratories with excellent concordance between the laboratories. Samples labelled with the unique study ID only will be handled in the UCL laboratory and results, on a spreadsheet, will be returned to the GOSH laboratory where the results will be entered into the master database. NO DATA will be transferred from GOSH to UCL. When new assays become available they will also be evaluated in the UCL laboratory with the same arrangements for sample and data transfer.

At the end of the study the samples will be stored at -70^o^C in the freezers of the Great Ormond Street Camelia Botnar Laboratories for future research. Future studies may involve genetic testing on the samples and this has been highlighted on the consent form. However independent ethical, institutional and regulatory approval will have to be sought before those studies and access to the samples are permitted. The consent form clearly states that staff may need to be asked to re-consent in the future before future genetic testing. We would also like to use the collected samples in the future to improve our diagnostic test and compare it to other tests that are developed over time and may be better.

The study will not share samples with collaborators that are linked with any identifiable data, although we may use non-identifiable samples to collaborate with international colleagues to enabled improved testing of SARS-CoV-2. This will be done once ethical, institutional and regulatory approvals are in place and under appropriate agreements as necessary.

# Financial Information and Insurance

Funding has been provided by GOSH to test the first 1000-1250 staff members and undertake the baseline assessment. However we are actively seeking funding to allow for this cohort to be followed up over time. As this study is non-interventional observational prospective cohort study we do not anticipate any adverse events other than those associated with a blood test. As with any research undertaken at GOSH and UCL ICH, cover for negligent harm will be provided by the Great Ormond Street Hospital for Children NHS Foundation Trust through the Clinical Negligent Scheme for Trusts (CNST). No-fault compensation insurance cover for any non-negligent harm will be provided by University College London.

# Publications Policy

All individuals who have made substantial intellectual, scientific and practical contributions to the study and the manuscript will be credited as authors and this will be overseen by the Chief Investigator, co-PI's and the Sponsors. In all cases where journal policies permit, all investigators who contribute patients to the study will be acknowledged.

The results of the study will be published in open access peer-reviewed scientific journals. Internal reports will be published on the UCL Institute of Child Health Web Pages which ware publicly assessible. We will also present our study findings at ECCMID and provide writted feedback of the study recruits by email.

# 19 Appendix A: Study Flow Charts

[figure not shown]

# Appendix B: Schedule of Procedures

| **Procedures** | **Baseline Screening, Baseline Blood Tests and Follow-Up** | | | |
| --- | --- | --- | --- | --- |
|  | **Screening** | **Baseline Blood Tests** | **Follow-Up N=200 Cases (x18)** | **Follow-Up N=800 Comparison Group (x13)** |
| Informed consent | X |  | X | X |
| Demographics | X |  | X | X |
| Medical history | X |  | X | X |
| Concomitant medications | X |  | X | X |
| Physical examination |  |  |  |  |
| ECG |  |  |  |  |
| Laboratory tests |  | X | X | X |
| Eligibility assessment | X |  |  |  |
| Randomisation |  |  |  |  |
| Intervention |  |  |  |  |

